[figure not shown]

| **Protocol:** Physiotherapeutic interventions for pain relief in women in the immediate postpartum period following cesarean section  **Project:** “Stimulating delivery in the immediate postpartum period following cesarean section to prevent pain resulting from antalgic postures: a randomized clinical trial.”  **Prepared by the research team:**  **PhD. [name]**  **[name] [name]**  **Collection Center:**  - Federal University of Triângulo Mineiro – University Hospital of the Federal University of Triângulo Mineiro  * This protocol to be tested is based on physiotherapy intervention protocols in the postoperative period of cesarean section in which the proposed activities led to a reduction in pain scores.  It is estimated that the application of this protocol will take approximately 40-50 minutes and should be started after the collection of sociodemographic, clinical, and obstetric data and after the signing of the Informed Consent Form, or the Informed Consent Form when applicable. |
| --- |
| **Responsible parties**: PhD [name] and members of the project team. |
| **Target Audience:** Postpartum women who underwent cesarean section and were assisted in the institution's postpartum wards. |
| **Objectives** |
| To perform physiotherapy interventions to relieve pain during movement in women in the immediate postpartum period following a cesarean section and to evaluate their effectiveness. |
| **Description** |
| **Location:** Rooming-In Wards. |
| **Team required:** researcher trained for intervention. |
| **Inclusion criteria:** All postpartum women who underwent cesarean section, are over 15 years old, hemodynamically stable, conscious, oriented, in good clinical condition according to their medical records, whose procedure was performed more than eight hours prior, after having their urinary catheter removed, and who ate after surgery will be included in the study. |
| **Equipment needed:** a folded sheet or a pillow or cushion if available, a simple chair and/or a chair with arms, if available. |
| **Materials:** 1 small bottle or container with 70% alcohol and/or sink, water and soap for hand hygiene for the researcher; 1 clipboard; pen; Informed Consent Form/Informed Consent Form. |
| **Prerequisites for the protocol** |
| Daily, the researcher will contact the responsible nurse, check the list of hospitalized postpartum women, and, based on the census, identify eligible postpartum women (those who underwent cesarean section).  At the time of contact 0 (allocation), postpartum women over 16 years of age must be hemodynamically stable, conscious and oriented, in good clinical condition, as documented in their medical records, and hospitalized in the Rooming-In Unit. The surgical procedure must have been performed more than eight hours prior, the urinary catheter must have been removed, and the woman must have eaten after surgery.  After identifying eligible participants, the researcher will go to the ward where they are hospitalized. Postpartum women will be informed of the study's objective, and the possibility of participating in the control/intervention groups will be emphasized. If they agree to participate, they will sign the Informed Consent Form.  If the participant is 15-18 years old, she must give her consent, and the Informed Assent Form must be signed by her legal guardian after the necessary explanations.  After signing, the researcher will give the participant one copy of the form and keep the second copy.  Once participation is consented to, the researcher will contact the randomization center defined for the study (which will have the randomization list of participants) via WhatsApp® and indicate the participant's number, receiving the participant's allocation (control/intervention) from the center.  This protocol was not designed to be applied to: women who experience complications/incidents during or after childbirth; who have a clinical contraindication or medical diagnosis of cognitive impairment that prevents participation, as well as those who need to use opioid medications to control pain. These criteria were not designed for exclusionary purposes, but rather to assess the feasibility of the intervention and the follow-up required for the Clinical Trial. However, if the need for postpartum women not included in this protocol is detected, they will receive guidance from the institutional or research team. |
| **Protocol description** |
| Researchers will contact unit nurses to select eligible participants for the study, using data from the daily census of hospitalized patients and medical records. Once the inclusion and exclusion criteria have been verified, they will proceed to the AC wards.  Good morning (or good afternoon), [name] (name of the postpartum woman)! How are you?  Could we speak with you?  My name is [name]. I am a physiotherapist and doctoral student, and I am part of a research team investigating physiotherapy interventions to reduce postpartum pain during movement. I would like to invite you to participate. Could we discuss the study?  **Negative response** – thanks for your attention, and record the refusal.  Affirmative response – that's great! I will read the consent form, which will explain the study. If you have any questions, feel free to interrupt me at any time. At the end of the reading, if you agree to participate, please sign this form in duplicate. I will keep one copy, and the other will remain with you. I inform you that during the research, we will take some notes, should you consent to participate.  **The Informed Consent Form is read aloud.**  The researcher will provide the necessary time for the postpartum woman to discuss her participation with her family/companion.  After obtaining the signature, the form is given to the postpartum woman.  **Precautions before data collection and intervention:**  Ensure the postpartum woman and the newborn are safe (by preventing falls or other incidents).  Ensure there are no physical barriers during contact.  The researcher's cell phone should be on silent mode or turned off at this time.  The researcher who will perform the intervention should be without a watch and always attentive to eye contact with the postpartum woman. For safety reasons, the researcher should not wear jewelry.  The researcher should touch her appropriately, always asking permission, and narrate what is being observed understandably.  Before starting the research itself, the researcher should offer practical support to the postpartum woman – checking whether she has eaten, whether she needs to go to the bathroom, and whether she needs help with the newborn, among other things.  After identifying that she is comfortable, begin the following procedures:  **Procedures:**  The researcher will begin data collection with sociodemographic, clinical, and obstetric questions. These may be supplemented with information from the medical record, if necessary.  Afterwards, she will inquire about functional limitations for each movement type and the pain score during performance. To measure pain, the Numerical Pain Rating Scale (NPRS) will be used. The postpartum woman will be instructed to rate her pain for each activity on a scale of 0 to 10, where 0 indicates no pain, and 10 indicates the worst possible pain.  She will be asked whether she can perform the movement and whether she feels pain while doing so. It is important to clarify that the risk of thrombosis in the lower limbs will be assessed using the Homans Sign and Flag Sign tests before proposing the exercise in item 10 (feet). The following activities will be evaluated:  1. Breastfeeding while lying down  2. Changing from lying down to standing next to the bed  3. Walking  4. Changing and bathing the newborn  5. Breastfeeding/feeding the newborn in a seated position  6. Sitting down/standing up from a chair  7. Sitting down/standing up from the toilet  8. Coughing/sneezing  9. Bathing  10. Active foot movement  If the person reports pain, they will be asked to indicate the point of pain on the image to pinpoint its location.  [figure not shown]  * Figure in Portuguese as per original image.  You will also be asked to describe the sensation of pain, according to the McGill Pain Questionnaire.  **McGill Pain Questionnarie**  [figure not shown]Some words that I am going to read describe your current pain. Tell me which words best describe your pain. Choose only one word from each group, the one that best describes your pain (questionnaire adapted for the Portuguese language by Pimenta and Teixeira, 1996.  * Figure in Portuguese as per original image. NÚMERO DE DESCRITORES ÍNDICE DE DORSENSORIAL...................... SENSORIAL.....................   AFETIVO........................... AFETIVO.........................  AVALIATIVO................... AVALIATIVO.................  MISCELÂNIA................... MISCELÂNEA................  **TOTAL........................... TOTAL..........................**  * Figure in Portuguese as per original image.  Subgroups 1 to 10 represent sensory responses to painful experiences (traction, heat, torsion, among others); the descriptors for subgroups 11 to 15 are affective responses (fear, punishment, neurovegetative responses); subgroup 16 is evaluative (evaluation of the overall experience), and subgroups 17 to 20 are miscellaneous.  After collecting this data, the intervention will be carried out according to the following protocol:  **Breastfeeding while lying down:** the postpartum woman will be instructed to adopt the supine position, with or without elevating the head of the bed, respecting her comfort. If the head of the bed is elevated, a pillow or similar object can be placed to support the spine. The newborn should initially be held in one arm, with support from a pillow or similar object under the newborn, on the ipsilateral side to the breast that will be offered. The other arm remains free to assist when necessary. Alternatively, the lateral decubitus position can be adopted with the head supported by a pillow or similar object, or with one arm supporting the head. The other arm can be used to hold the newborn. The head of the bed should be slightly inclined or straight, and the legs can be in semi-flexion, flexion, or extension.  **Changing from a lying to a standing position beside the bed:** A postpartum woman, in a supine position with the bed at an angle, should turn onto her side (the chosen side position can be the one preferred by the postpartum woman) and raise her trunk, supporting herself on the upper limb on the same side as the one supporting her on the bed. At the same time, she should move her lower limbs off the bed before assuming a sitting position. Breathing should be calm, and exhalation will be required during the effort to raise the trunk. In the sitting position, the trunk should be straight, the feet flat on the floor, and the shoulders level, without protrusion. Inhale deeply, drawing air in through the nose and exhaling through the mouth 3 times. Then, place your hands on the bed laterally to your body, directing the force to your legs, and exhale as you stand up. Repeat the inhalation and exhalation 3 times. If the postpartum woman has difficulty performing these movements with the bed not inclined, she can use the head of the bed elevated until she can sit up, then move by rotating her torso and legs to place them off the bed. All movements should be performed during exhalation.  **Walking:** while walking, keep your torso straight, arms along your body, and shoulders relaxed and symmetrical; inhale through your nose and exhale through your mouth at a calm pace; walk for approximately 5-8 minutes.  **Changing and bathing the newborn:** to guide the appropriate height for these activities, the crib in the rooming-in area will be used: patient standing, upright posture with slight flexion of the spine if necessary, the changing and bathing area should be at elbow level, and the patient should not have to bend over to perform the activity;  **Breastfeeding/feeding the newborn in a seated position:** the patient will be instructed to position herself in a chair or similar, with her spine straight and supported by the backrest or, if unavailable, against the wall, and, if available, to use pillows to help support her back. Her feet should be flat on the floor, with her knees at approximately 90°, shoulders level and relaxed, and her cervical spine also relaxed. The newborn can be supported on a pillow or similar item on the mother's lap, where she will cradle him with her arm. The mother will be instructed not to keep looking at the newborn all the time, so that her cervical spine does not remain flexed, avoiding pain. If preferred by the mother, she can adopt the inverted position for the newborn, holding him sideways under the flexed arm with his head supported by the mother's open hand, positioning the newborn's face towards the breast. The baby's back will rest on the mother's forearm.  **Sitting/Standing from a chair:** Begin the activity by using the chair's arms, if available, and the strength of your lower limbs to stand up. Exhale as you sit/stand so that the force is not applied to the abdominal region (the scar). If necessary, support the surgical scar with one hand (palm) and the other hand on the chair to maintain balance while sitting/standing.  **Sitting/Standing from the toilet: To sit:** Concentrate the force on your lower limbs and slowly bend your torso, lowering yourself while exhaling until you reach the toilet. If necessary, use one hand to support yourself on the toilet while lowering yourself onto it. **To stand:** Support yourself firmly on your lower limbs and, if necessary, use one hand (palm) to support the surgical scar. If the strength is insufficient, use one hand to support yourself on the toilet.  **Coughing/sneezing:** Use your hands, palms flat and one on top of the other, to support the scar. A folded towel or pillow/cushion can also be used for support before coughing or sneezing.  **Bathing:** Keep your torso straight, inhale through your nose and exhale through your mouth, support the scar with one hand while using the other to clean your hands. To clean your lower limbs, use a support (chair or similar, if necessary) and raise the limb closest to your hands, avoiding bending your torso.  **Active foot movement:** Patient in supine position, lower limbs above heart level with the bed elevated in the lower limb region, perform alternating active dorsiflexion and plantarflexion movements: 10 repetitions, 2x/day.  After applying the interventions, satisfaction with them will be evaluated using a Likert scale, asking:  How did you feel about the guidance on performing the activities?  ( ) not satisfied ( ) somewhat satisfied ( ) satisfied ( ) very satisfied  The researcher will not take notes during the intervention.  If the baby wants to breastfeed during the intervention, the intervention should be postponed until after breastfeeding.  After the intervention, the researcher will thank the participants, say goodbye, and emphasize that they will return the following day (24 hours after the intervention). If any changes were made to the ward layout, they should be rearranged.  24 hours after the initial contact, the researcher will ask again whether she can perform the movements and record the pain scores for each movement described. If she experiences pain, she will ask her to indicate its location and characteristics.  At the end of data collection, the researcher will hand over a folder containing the instructions for the patient to take home, thank her, and say goodbye. Afterwards, she will check the medical record for analgesic consumption during the period and painful complaints recorded in the medical record. |

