**Unexpected situations**

| **Unexpected situations** | **Solutions** |
| --- | --- |
| **Operacional*** | |
| Complications with the postpartum woman during collection/intervention (orthostatic hypotension, malaise) | Stop collecting/intervening, stabilize the postpartum woman, and call a professional from the sector for evaluation. |
| Complications with the newborn (crying, choking, or others) and the postpartum woman being unaccompanied. | Ensure the newborn is safe.  Provide practical assistance.  Call a team member if necessary.  Ensure the postpartum woman is accompanied before starting the collection/intervention. |
| Incidents with the newborn (crying, choking, or others) | Stop collection/intervention, stabilize the newborn, and call a professional from the sector for evaluation if necessary. |
| Communication difficulties (due to low level of education or difficulty understanding terminology) | - Establish a bond with the postpartum woman - Pay attention to signs that the postpartum woman is not understanding or is somehow uncomfortable - Try to make her as comfortable as possible - Simplify the way the guidance is given according to her understanding (comprehension of the words) - Check the companion's understanding and ask for their help. |
| Giving up mid-data collection/intervention | Establish a connection with the postpartum woman, and if, even after explanations, she does not wish to participate, do not insist. |
| The nursing or medical team needs to perform a procedure on the postpartum woman or newborn. | Confirm with the team whether the postpartum woman or newborn will be undergoing any procedures at the time the sample collection/intervention will take place. |
| Visit from other professionals (social worker, nutritionist, physiotherapist) | Confirm with the team whether the postpartum woman will be attending any multidisciplinary appointments at the time the sample collection/intervention will take place. |
| Visiting hours | Confirm visiting hours and conduct data collection/intervention before or after visiting hours. |
| Emergencies involving the postpartum woman, newborn, or the nursing department. | In emergencies, cease collection/intervention, notify the team, assist only if requested, and leave the ward clear. |

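### As the protocol reads, the arm is disclosed to the researcher after consent and before baseline pain is scored, so the baseline can be elicited unmasked and early drop-outs are already randomised

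*Protocol*

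**What the plan says.** Under Prerequisites for the protocol, consent is the trigger for allocation: "Once participation is consented to, the researcher will contact the randomization center defined for the study". The contact is by WhatsApp, and it ends with the researcher "receiving the participant's allocation (control/intervention) from the center". The same section ties the eligibility conditions to a contact that it labels as allocation: "At the time of contact 0 (allocation".

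The bedside sequence is under Protocol description. After the signature come precautions, including "The researcher's cell phone should be on silent mode or turned off at this time". The Procedures then start: "The researcher will begin data collection with sociodemographic, clinical, and obstetric questions". Pain follows: "Afterwards, she will inquire about functional limitations for each movement type and the pain score during performance". It is rated 0 to 10 for each of ten activities, then its location and McGill description are taken. The next step is the intervention. The researcher returns at 24 hours to score pain again.

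Three other places matter:

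- The opening table lists one staff role, a researcher trained to intervene.
- The Intervention plan table makes the content depend on the baseline answer. A woman without pain or difficulty gets breathing instruction only; a woman with pain gets guidance on the ten activities as well.
- The Unexpected situations table foresees "Giving up mid-data collection/intervention" and tells staff not to insist.

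**The concern.** A baseline is useful because the assigned arm cannot have influenced it. If the arm is known before the baseline is taken, that protection is gone. These scores are elicited by interview, activity by activity, so prompting and clarification can differ between arms without anyone intending it. A difference created in this way carries into any analysis that uses the baseline.

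Two features of this trial add to the problem. In the intervention arm the baseline answer decides what the woman receives, so an arm-aware interview can also affect delivery. And if allocation comes first, a woman who stops during the interview counts as a post-randomisation loss with an incomplete baseline, whereas with the order reversed she would not have been randomised. No analysis plan can restore an unmasked baseline afterwards.

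**Working it through.** **Order of steps.** The protocol gives no figure to reproduce, so the first check sets its sections side by side.

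1. Consent is signed (Prerequisites; Protocol description).
2. The centre is contacted and returns the arm to the researcher (Prerequisites).
3. Phone silent or off (Precautions).
4. Sociodemographic, clinical and obstetric questions (Procedures).
5. Ten pain scores, location, McGill (Procedures).
6. Intervention (Procedures).
7. Pain scored again at 24 hours (Procedures).

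Step 2 appears only under Prerequisites, where consent is its only stated trigger. Nothing between steps 5 and 6 mentions allocation. The opening table says the protocol starts after consent and after the sociodemographic, clinical and obstetric data, but it mentions neither allocation nor pain scores, so it does not settle the order. Allocation before baseline is therefore the natural reading, and no section contradicts it.

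**Illustrative size.** The protocol states no SD, sample size, correlation or analysis model. All inputs here are assumptions: SD 2.5 at both times, n = 50 per arm, two-sided 5% test, correlation r between baseline and 24 hours, and a spurious shift d in one arm's baseline mean.

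False-positive rate = Φ(b/se − 1.96) + Φ(−b/se − 1.96), where b is the bias in the contrast and se = SD of the analysed quantity × √(2/n).

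*Change score.* b = d. SD of change = 2.5 × √(2(1 − r)), which is 2.5 at r = 0.5. Then se = 2.5 × √(2/50) = 0.5.

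| d | b/se | Rate |
|---|---|---|
| 0.1 | 0.2 | 5.5% |
| 0.2 | 0.4 | 6.9% |
| 0.5 | 1.0 | 17.0% |

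The correlation matters. With d = 0.5:

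- r = 0.3: SD of change 2.96, se 0.592, rate 13.5%.
- r = 0.7: SD of change 1.94, se 0.387, rate 25.2%.

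SD and sample size matter too. With d = 0.5 and r = 0.5:

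- SD 3, 30 per arm: se 0.775, rate 9.9%.
- SD 2, 80 per arm: se 0.316, rate 35.3%.

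*Baseline-adjusted.* With r = 0.5 and equal SDs the slope is 0.5, so b = 0.5 × d. Residual SD = 2.5 × √(1 − 0.25) = 2.165 and se = 2.165 × √(2/50) = 0.433. For d = 0.5, b = 0.25, b/se = 0.577 and the rate is 8.9%.

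*24-hour score alone.* The baseline does not enter, so b = 0 from this source and the rate stays at 5%. Losses between allocation and baseline still apply.

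**The case against.** No single sentence gives the full order; it has to be joined from two sections. The supporting clues are weak. The contact 0 label marks when eligibility must hold and comes before the consent text. A phone on silent can still receive a message. The plural "researchers" and the mention of the researcher who performs the intervention leave room for different people at different steps. The woman gives the rating and chooses the McGill words herself. No change score or baseline adjustment is fixed, and nothing in the protocol supports a 0.5-point shift.

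Much of this stands. It limits how firmly the order can be asserted and makes the figures illustrations only. It does not remove the point: consent is the only trigger given for allocation, no later allocation step exists, and no division of roles or masking is stated.

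A reader might infer more than the documents support:

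- *That concealment at enrolment is broken.* The list stays with the centre and the arm is returned only after consent.
- *That the woman knows her arm when she rates her baseline pain.* The protocol does not say so.
- *That women who leave during baseline contribute no data.* Sociodemographic, clinical and obstetric questions come first, so partial data would often exist. The contingency row also covers the intervention and gives no rate.
- *That every analysis is biased by a shifted baseline.* A comparison of 24-hour scores alone is not.

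**Conclusion.** The point holds as a should-fix. The sections read together place disclosure of the arm between consent and the baseline pain assessment, and nothing keeps the arm from the person who scores the baseline. That exposes a change-score analysis fully, a baseline-adjusted analysis in part, and every analysis to losses between allocation and baseline. Whether a shift would occur, and how large it would be, cannot be learned from the protocol. The size of those losses cannot be estimated either. The calculated rates rest wholly on the assumed SD, sample size, correlation and shift: small shifts do little, and the largest ones considered do real damage. This is not grounds for calling the trial's randomisation invalid.

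**What to change.** Make four linked edits:

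1. Under Prerequisites, state that the centre is contacted only after the last baseline entry (ten pain scores, location, McGill) is recorded and closed, with a completion time earlier than the allocation message.
2. Under Procedures, insert the allocation step immediately before the sentence that introduces the intervention.
3. Amend the phone precaution to allow the message at that point; otherwise it conflicts with the new order.
4. Rename contact 0 so that it is no longer called allocation.

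This needs no extra staff, visits or participants. The cost is a short wait at the bedside for the centre's reply. The 24-hour scores are also recorded by the researcher with no masking stated; that is a separate issue, and this change does not cure it.

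### Nothing separates or masks the 24-hour pain interview from delivery of the intervention, so the between-arm pain comparison is at risk of interviewer and courtesy bias

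*Protocol*

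**What the plan says.** The relevant statements stand in three parts of the protocol.

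- **Allocation.** Under Prerequisites for the protocol, the researcher at the bedside contacts the randomization center once consent is given, "receiving the participant's allocation (control/intervention) from the center". When the study is explained, "the possibility of participating in the control/intervention groups will be emphasized".
- **Introduction.** The recruitment script under Protocol description has the researcher say that she is a physiotherapist and that "I am part of a research team investigating physiotherapy interventions to reduce postpartum pain during movement".
- **Delivery.** The opening summary puts the contact time as follows: "It is estimated that the application of this protocol will take approximately 40-50 minutes". The team required is given only as a "researcher trained for intervention".
- **Outcome.** Under Procedures, the researcher collects the baseline pain score for each of ten movements on a 0-10 numerical scale. The guidance follows. Afterwards the researcher is to "say goodbye, and emphasize that they will return the following day". At 24 hours "the researcher will ask again whether she can perform the movements and record the pain scores for each movement described". Where pain is present, its location and character (the McGill words) are collected as well. The researcher then checks the medical record for analgesic use and recorded pain complaints.

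The protocol does not mention a separate assessor, masking of whoever asks the questions, or scales that the woman completes herself.

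**The concern.** The stated objective is to relieve pain during movement and to evaluate whether the intervention does so. The measure that answers this is a number the woman gives aloud to an interviewer. Such a rating can shift with who asks, how the question is put, and what the woman believes the interviewer hopes to hear.

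If the interviewer spent 40 to 50 minutes helping women in one arm and knows who they are, two influences can enter. The interviewer may prompt or record differently by arm, and the woman may be reluctant to tell the person who helped her that it did not work. Both would probably lower reported pain in the intervention arm. A difference produced in this way looks the same in the pain scores as a treatment effect, and no analysis model removes it. It has to be prevented by the way the scores are obtained, which this protocol fixes.

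**Working it through.** **Step 1: who knows the arm, who delivers, who asks.**

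| Task | Who, according to the protocol | Where |
| --- | --- | --- |
| Obtains consent and receives the allocation | the researcher | Prerequisites for the protocol |
| Asks baseline pain | the researcher | Procedures |
| Delivers the guidance | a researcher trained for it | Description, Team required; Procedures |
| Takes leave and announces a return | the researcher, after the intervention | Procedures |
| Asks again and records pain at 24 hours | the researcher | Procedures |

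The wording about returning and asking again joins the last three rows to one role. No row is given to someone else, and no row is masked.

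**Step 2: how sensitive a pain comparison is to a reporting shift.** The protocol gives no sample size, SD, significance level or effect size, so there is no figure of its own to reproduce. All inputs here are assumptions chosen for illustration: SD 2.5 points, 50 women per arm, two-sided 5% test, normal approximation, no true effect.

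Standard error of the difference in means:

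SE = SD × √(2/n) = 2.5 × √(2/50) = 2.5 × 0.2 = 0.5

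If reporting alone shifts the intervention mean by b points, the chance of a significant result in either direction is

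Φ(b/SE − 1.96) + Φ(−b/SE − 1.96)

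| b (points) | b/SE | Calculation | False-positive rate |
| --- | --- | --- | --- |
| 0 | 0 | 2 × Φ(−1.96) | 5.0% |
| 0.25 | 0.5 | Φ(−1.46) + Φ(−2.46) | 7.9% |
| 0.5 | 1.0 | Φ(−0.96) + Φ(−2.96) | 17.0% |
| 1.0 | 2.0 | Φ(0.04) + Φ(−3.96) | 51.6% |

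**Step 3: range over the assumptions.** For a shift of 0.5 point:

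- SD 3 and 30 per arm: SE = 3 × √(2/30) = 0.775, b/SE = 0.645, rate 9.9%.
- SD 2 and 80 per arm: SE = 2 × √(2/80) = 0.316, b/SE = 1.581, rate 35.3%.

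A larger trial makes this worse, because the standard error shrinks and the bias does not. The table shows what a shift of a given size would do. It does not estimate the shift.

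**The case against.** Several points can fairly be raised on the other side.

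- **One person in every role is an inference.** The protocol refers to members of the project team, uses the plural for researchers, and at one place singles out the researcher who will perform the intervention. The team entry says who is needed to apply the intervention, not who assesses at 24 hours. This stands in part. A reader might infer that a single individual certainly does everything, and the text does not go that far. It does assign the 24-hour questions to the same role, and it gives them to nobody else.
- **Not every outcome depends on the interview.** A reader might infer that the whole evaluation rests on what women say. Analgesic use and recorded complaints come from the medical record and give a partial cross-check, although the same researcher extracts them. They do not replace the pain scores.
- **Satisfaction.** A reader might extend the point to the satisfaction item ("not satisfied ( ) somewhat satisfied ( ) satisfied ( ) very satisfied"). That does not hold as a between-arm bias. The item asks about the guidance, directly after it is given, so it suits women who received guidance and offers no clear contrast with controls. No asker is named either.
- **The difference in contact is not fully described.** Control-arm contact is not set out in this document, and the explanation of the study's aim goes to everyone. The 24-hour score also comes a day after the guidance. This limits how firmly the direction can be stated.
- **Bias is not demonstrated.** This is correct. The direction is likely and the size is unknown.

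None of these points supplies a separate assessor, a masked one, or self-completion.

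**Conclusion.** The point holds as a risk of bias. As written, the researcher who knows the allocation and, on the plain reading, delivers the intervention returns at 24 hours to obtain and record the pain scores. Nothing separates or masks outcome collection. The comparison of pain between arms is exposed to interviewer and courtesy effects that probably favour the intervention and could largely be avoided.

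The size cannot be derived from the protocol. The rates of about 8%, 17% and 52% rest entirely on the assumed SD, sample size and shift, and show sensitivity only. The documents do not support saying that the result will be biased, or by how much. The change is worth making because it is cheap and protects the measure that answers the trial's objective.

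**What to change.** **Change to Procedures.** In both arms, each woman marks the ten numerical pain scores herself on a printed form coded with her participant number and places it in a sealed envelope. This is done in the same way at baseline and at 24 hours, so that the two measurements share one mode. At 24 hours she completes it before any conversation with the researcher.

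**Where help is needed, and for pain location and the McGill words at 24 hours.** Use an existing project-team member who did not treat the woman and is not told her arm, where one is available. The companion is a poor substitute, being likely to know what she received. If the team already intends to separate delivery from assessment, the protocol should say so and state who is masked.

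**Cost.** One printed form and envelope per woman at each of two time points, and some swapping of roles within the present team. Some women with low literacy will need help; the section on unexpected situations already anticipates communication difficulties. Participants remain aware of their arm, so expectation bias stays. The change removes only the part due to the interviewer. It alters no treatment.
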